### Work plan

Before the trial begins, the study protocol will be presented to all research team members in a special meeting. A training session lasting 3–4 h will include a review of the inclusion and exclusion criteria, provide instructions regarding interventions and the procedure to use to fill out the Case Report Form (CRD), as well as assessing the ethical requirements for the trial. The protocol to be used to collect information from each patient at each study visit will include (see Additional file 2: Table S1):

•**Selection visit (screening)**

Assessment of inclusion/exclusion criteria

Signing informed consent form

•**Visit 1 (baseline).***If patients agree to participate in the study at the selection visit, all scheduled activities for visit 1 can be performed at the selection visit. If patients require time to think about participating, these scheduled activities will be performed at visit 1.*

Randomization process

Collection of demographic data, including date of birth, sex, and place of usual care

Risk factors for PrU, using the Braden scale

PUSH Scale registry, including area of each lesion (width × length), volume of exudates and tissue type

PrU photographic registry

Healing process registry: reason to change dressing, time treated by the nurse, materials used

Training about transverse care (positional changing and pressure reduction)

Recording of concomitant medications

Recording of adverse events

•**From Visit 2 to Visit 7 (Follow-up)**

Assessment of inclusion/exclusion criteria

Assessment of transverse interventions, from each patient’s diary and nursing files

PUSH Scale registry, including area of each lesion (width × length), volume of exudates and tissue type

Healing process registry: reason to change dressing, time treated by the nurse, materials used

Recording of concomitant medications

Recording of adverse events

•**Between visits.***The study protocol includes 8 study visits. If patients require a change of dressing, between visits,it must be recorded in the CRF, with the following information collected.*

Date of dressing change

Reason for dressing change (exudates, lack of adherence, other reasons)

Time treated by the nurse (mm:ss)

Materials used

•**Visit 8 or End of study**

PUSH Scale registry: diameter of each lesion (width × length), volume of exudates and tissue type.

Completion of the dressing scale comfort instrument by patients and study nurses

Braden scale

PrU photographic registry

Recording of concomitant medications

Recording of adverse events

This study will last 8 weeks (8 visits) or until the ulcer heals, whichever comes first. The protocol for Visit 8 can include 3 different situations:

1. *PrU-II heals before week 8 (visit 8).* If complete healing is observed at an earlier visit, the nurse will perform the activities described for that Visit plus those described for Visit 8.

2. *PrU-II does not heal by week 8 (visit 8)*. The nurse will perform all the activities described for Visit 8.

3. *The patient presents some withdrawal criteria before week 8 (Visit 8).* The nurse will perform all the activities described for the earlier visit, as well as those described for Visit 8.

### Statistical analysis

#### Intention to treat analysis (ITT)

All statistical calculations will be based on ITT analysis, including all patients randomized, whether treated or not, and including all patients who have withdrawn prematurely. This approach reduces any bias that may occur when participants not receiving assigned treatments are excluded from analysis. All tests will be two-sided and α-values of 0.05 will be considered statistically significant.

#### Descriptive analysis of the patients

The trial involves a descriptive analysis of the baseline characteristics of patients in both treatment arms. Quantitative variables will be reported in measures of central tendency (mean or median) and the corresponding standard deviation or interquartile range. Qualitative variables will be reported as proportions.

#### Baseline comparisons

Baseline qualitative variables in the two treatment arms will be compared using chi square tests (χ^2^), and quantitative variables using Student’s t-tests. Non-parametric tests will be used when distributions are not normal.

#### Comparative analysis

In a bivariate analysis, a χ^2^ test will be used to assess whether the percentage of healed PrU-IIs differs significantly in the two treatment arms. Mean changes in PrU size will be compared using Student’s t-tests for normal distributions or the Mann-Whitney U test against the usual null hypothesis (non-normal distributions): (initial area-final area)*100/initial area). In addition, 95% confidence intervals will be calculated to assess the clinical significance of treatment.

A logistic regression model adjusted for potential confounders will be performed when patients are not equally distributed in both treatment arms. Relative and absolute risk reduction and number needed to treat, defined as the estimated number of ulcers needed to be treated with the chosen dressing for one additional ulcer to be healed will be estimated, along with their corresponding 95% CIs.

Time to healing in the two treatment arms will be calculated by the Kaplan-Meier method and compared using the log-rank test. A Cox regression model of proportional risks will be used when the models require adjustment for any statistically significant baseline variable.

Finally, a partial economic evaluation will be performed, including direct costs such as number of dressings used per patient, additional dressings used, materials used, labor cost per cured ulcer and further treatment cost. The overall differences in mean costs and effects between treatments will be calculated using Student’s t-tests.

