**Methods/design:**

This paper describes the development and evaluation protocol of a randomized clinical trial of two parallel treatment arms. A total of 820 patients with at least 1 PrU-II will be recruited from primary health care and home care centers. All patients will receive standardized healing procedures and preventive measures (e.g. positional changes and pressure-relieving support surfaces), following standardized procedures. The main outcome will be the percentage of wounds healed after 8 weeks. Secondary outcomes will include cost-effectiveness, as evaluated by cost per healed ulcer and cost per treated patient and safety evaluated by adverse events.

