### Setting and eligibility criteria

This study will recruit patients who receive primary health assistance, including patients able to attend the primary health center or receive health assistance in homes, nursing-homes and non-acute long term hospitalization centers. Each patient must present with at least one PrU-II.

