### Randomization

Participants will be enrolled consecutively by their study nurse. Each participating center will have a unique randomization list. This sequential randomization will be generated in blocks of 12, up to a maximum of 24 recruited patients per center (see Additional file 1: Figure S1).

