### Sample size

Assuming that 30% of patients in the polyurethane arm will show healing of PrU-II at 8 weeks, an alpha risk of 5%, a beta risk of 20% with bilateral contrast and a loss to follow-up of 15%, 410 individuals will be required in each treatment arm to detect a ≥10% difference in healed ulcers [22,23].

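### Allocation is stratified by centre, but the chi-square test of healing and the log-rank test ignore centre; if healing differs between centres, these tests are conservative and some precision is lost

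*Protocol article*

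**What the plan says.** On allocation, the Randomization section of the protocol article says: "Each participating center will have a unique randomization list". It continues: "This sequential randomization will be generated in blocks of 12, up to a maximum of 24 recruited patients per center". Centre is therefore a stratification factor, and the arms are kept close to balance within each centre.

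On analysis, the Comparative analysis section says that a chi-square "test will be used to assess whether the percentage of healed PrU-IIs differs significantly in the two treatment arms". Time to healing is compared with a log-rank test. Neither test is described as stratified. The section allows adjustment in two situations only: a logistic model if the arms turn out unequal, and a Cox model if a baseline variable is statistically significant. Centre is named in neither rule.

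On setting, the Setting and eligibility criteria section admits patients who can attend a primary health centre and those who "receive health assistance in homes, nursing-homes and non-acute long term hospitalization centers".

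**The concern.** When arms are balanced within centres by design, differences in healing between centres cancel out of the comparison of arms. An unstratified chi-square still counts them as random error. Its standard error is then larger than the true sampling error of the difference, so P values are somewhat too large and intervals somewhat too wide.

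The adjustment rules do not repair this. They respond to imbalance, and centre is the factor that the blocks keep balanced, so the rules tend to leave out the one variable that the randomisation gave a design reason to include. The article fixes both the tests and the triggers, so this is a stated choice and not a detail left to an unseen analysis plan.

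Differences between centres are plausible. The settings are mixed, each centre has only one or two study nurses who carry out all procedures, and pressure relief is delivered locally. What is at stake is precision that the stratified randomisation makes available and the analysis does not use.

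**Working it through.** **Inputs from the article.** Sample size section: "Assuming that 30% of patients in the polyurethane arm will show healing of PrU-II at 8 weeks"; two-sided alpha 5%, beta 20%, 15% loss; "410 individuals will be required in each treatment arm to detect a ≥10% difference in healed ulcers". Abstract: 820 patients in total. Randomization section: blocks of 12, at most 24 patients per centre.

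**Reproducing the plan's figure.** For 30% v 40%, with mean proportion 0.35:

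n = [1.96 √(2 × 0.35 × 0.65) + 0.842 √(0.30 × 0.70 + 0.40 × 0.60)]² / 0.10² = 356 per arm.

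356 × 1.15 = 409.4, which rounds up to the stated 410. After 15% loss, 410 × 0.85 = 348 evaluable per arm, with 79.1% power. This is the benchmark for the power figures below.

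**Number of centres.** 820 / 24 = 34.2, so at least 35 centres, and more if centres do not fill.

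**Mechanism.** Let the ICC be the share of the outcome variance p(1 − p) that lies between centres. With n per arm, balanced within centres and no treatment effect:

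- variance used by the chi-square: 2p(1 − p)/n
- true variance of the difference: (1 − ICC) × 2p(1 − p)/n
- true alpha: 2[1 − Φ(1.96/√(1 − ICC))]
- interval width relative to the correct width: 1/√(1 − ICC), that is 1.03, 1.05 and 1.12 at ICC 0.05, 0.10 and 0.20

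**Simulation with full centres.** 20,000 trials per scenario; 34 centres with 12 per arm (816 patients); beta-distributed centre healing rates with mean 30%; a common odds ratio giving 40% overall in the other arm. The ICC values are assumptions, since the article gives none. CMH is the Cochran-Mantel-Haenszel test stratified by centre.

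| ICC | Alpha, formula | Alpha, simulated chi-square | Coverage of 95% CI | Power, chi-square | Power, CMH | Power forgone (points) |
|---|---|---|---|---|---|---|
| 0 | 5.0% | 5.0% | 95.0% | 78.9% | 78.6% | −0.3 |
| 0.02 | 4.8% | 4.4% | 95.5% | 79.2% | 79.6% | 0.4 |
| 0.05 | 4.4% | 4.4% | 95.6% | 79.1% | 80.4% | 1.3 |
| 0.10 | 3.9% | 4.0% | 95.9% | 80.2% | 82.8% | 2.6 |
| 0.20 | 2.8% | 3.0% | 97.0% | 81.4% | 87.4% | 6.0 |

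Alpha and coverage are under the null without loss; power is with 15% loss. With 15% loss, alpha is 4.8% at ICC 0.02, 4.4% at 0.05, 4.0% at 0.10 and 3.3% at 0.20. The Monte Carlo standard error is √(0.05 × 0.95/20,000) = 0.15 points for alpha and √(0.8 × 0.2/20,000) = 0.28 points for power. The CMH test held 4.9% to 5.2% at ICC 0, 0.05, 0.10 and 0.20 without loss.

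**Simulation with small, uneven centres.** The cap of 24 is a maximum, so centres may stay small. The set-up is 820 patients, blocks of 12, 15% loss and 30% v 40%. The centre sizes and the between-centre standard deviation (SD) of the log-odds are assumed; SD 0.5 corresponds to an ICC of about 0.05 and SD 0.8 to about 0.11.

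- Mean about 8 per centre, every centre its own stratum, chi-square v CMH: SD 0, 79.9% v 76.4%; SD 0.3, 80.1% v 77.4%; SD 0.5, 80.0% v 78.5%; SD 0.8, 80.0% v 80.5%.
- Mean about 5 per centre, every centre its own stratum, chi-square v CMH: SD 0.5, 80.1% v 74.9%; SD 0.8, 79.9% v 77.3%.
- Mean about 8 per centre, centres below 12 pooled (separate runs), chi-square v pooled CMH: SD 0, 79.1% v 78.9%; SD 0.5, 78.5% v 79.3%; SD 0.8, 79.8% v 81.2%.

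The log-rank test was not simulated. The same mechanism applies in the same direction, but its size is not quantified here.

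**The case against.** The strongest objection is that nothing is shown to be wrong with the validity of the planned test. Any error is on the safe side, the chi-square delivers 79% to 81% power after loss against the planned 80%, and the article gives no between-centre variation. At an ICC of 0.02 or less the difference in power is under half a point. All of this stands, and it limits the point to efficiency.

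The second objection is that stratifying by every centre can do harm. A stratified test gains little from tiny strata and nothing from strata with one arm only. With many small centres it loses about 2 to 3 points of power at low to moderate variation with a mean of about 8 per centre, and more with a mean of about 5. This also stands, as an objection to an unpooled remedy. Pooling centres below one full block removed the loss in the scenarios with a mean of about 8.

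Two stronger readings are tempting. A reader might infer that the P values are certainly too conservative, or that the trial loses its planned power. Neither follows: the first depends on variation that the documents do not report, and the power forgone is relative to a better test, not to the plan. A reader might also infer that ignoring centre inflates type I error, as in a cluster trial. It does not, because patients are randomised individually within centres.

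**Conclusion.** The point holds in conditional form. The factor used to stratify randomisation appears in neither main test, and the stated adjustment rules would not normally introduce it. If healing does not differ between centres, nothing is lost. If it does, the chi-square is conservative and its intervals are about 3% to 12% too wide over ICC 0.05 to 0.20, at a cost of about 1 to 6 points of power relative to a centre-stratified test. The gain is negligible up to ICC 0.02, small at 0.05 and material from about 0.10.

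These sizes rest on assumed ICCs and on nearly full centres. The direction follows from the design alone. The change is worth making because the trade is lopsided: with full centres it costs about 0.3 points if centres are alike and gains 1.3 points or more from ICC 0.05 upward.

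**What to change.** In the Comparative analysis section, replace the unstratified chi-square with a Cochran-Mantel-Haenszel test stratified by randomising centre. Report the Mantel-Haenszel risk difference and relative risk with 95% confidence intervals. State that centres recruiting fewer than one full block (12 patients) are pooled into a common stratum, under a rule fixed before unblinding, that is, before anyone has seen outcomes by arm. Stratify the log-rank test and the Cox model by the same strata, whatever baseline imbalance is observed.

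The cost is a few sentences and no new data, since centre is already known from the randomisation list. The downside is a negligible loss of power if centres do not differ. If many small centres were left unpooled the loss would be about 2 to 3 points, so the pooling threshold has to be part of the change.

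### Adjustment of the healing and time-to-healing analyses depends on observed baseline imbalance or significance, and the plan does not say whether the crude or the adjusted result governs

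*Protocol article*

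**What the plan says.** Under Baseline comparisons, the protocol article plans significance tests between the randomised arms: "Baseline qualitative variables in the two treatment arms will be compared using chi square tests", with t-tests or non-parametric tests for quantitative variables.

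Under Comparative analysis, the default tests are unadjusted. A chi-square test "will be used to assess whether the percentage of healed PrU-IIs differs significantly in the two treatment arms". For the time endpoint, "Time to healing in the two treatment arms will be calculated by the Kaplan-Meier method and compared using the log-rank test".

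Adjusted models are conditional:
- Healing: "A logistic regression model adjusted for potential confounders will be performed when patients are not equally distributed in both treatment arms".
- Time to healing: "A Cox regression model of proportional risks will be used when the models require adjustment for any statistically significant baseline variable".

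The article names no covariate, gives no criterion for unequal distribution, and does not say which result stands if the crude and adjusted analyses differ.

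The candidate covariates are recorded at Visit 1 for every patient (Work plan): place of usual care, Braden scale, and "PUSH Scale registry, including area of each lesion (width × length), volume of exudates and tissue type". Under Randomization, "Each participating center will have a unique randomization list".

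**The concern.** Under sound randomisation, any baseline difference between arms is a chance difference. A test of it answers no useful question, and its p-value says nothing about whether the variable predicts healing. Using imbalance or significance as the switch therefore selects covariates largely for the wrong reason. A strong predictor that is well balanced is left out and its precision is lost. A variable unrelated to healing can enter because it happened to differ.

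The second problem is discretion. When the switch is thrown, the trial has a crude and an adjusted result for the same endpoint, and nothing in the text ranks them.

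This is a rule that the article states, not a detail left to a fuller plan. An analysis plan that followed it would carry the weakness forward.

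**Working it through.** **1. The plan's own figure.** Inputs from Sample size: 30% against 40% healed, two-sided alpha 0.05, power 80%, 15% loss.

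n per arm = [1.96·√(2·0.35·0.65) + 0.842·√(0.30·0.70 + 0.40·0.60)]² / 0.10² = 356 after rounding up.

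356 × 1.15 = 409.4, so 410, as stated. (356/0.85 gives 419, close to it.) The size therefore rests on an unadjusted two-proportion test. With 15% lost, 410 × 0.85 gives about 348 evaluable per arm, where that test has 79% power by formula.

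**2. How often the switch is thrown.** Assume the trigger is a 5% between-arm test. One given variable then triggers in about 5% of trials and is left out in about 95%. For k independent variables, P(at least one) = 1 − 0.95^k. The article gives no k, so a range is assumed:
- k = 5: 1 − 0.774 = 23%
- k = 8: 1 − 0.663 = 34%
- k = 12: 1 − 0.540 = 46%

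**3. Effect on error and power.** Simulation with 348 per arm and one normally distributed baseline predictor. Marginal healing rates were 30% v 30% (12,000 runs) or 30% v 40% (8,000 runs). The rule adjusts only if the baseline t-test has p < 0.05. Predictor strength is assumed, because the documents give none. The odds ratio (OR) is per SD, and its direction does not matter.

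| | OR 1.65 | OR 2.7 |
|---|---|---|
| Type I error, chi-square | 4.7% | 4.7% |
| Type I error, adjust if imbalanced | 4.7% | 4.4% |
| Type I error, always adjusted | 4.9% | 4.9% |
| Type I error given imbalance, chi-square | 6.7% | 11.9% |
| Type I error given imbalance, adjusted | 6.2% | 4.9% |
| Power, chi-square | 79.9% | 79.5% |
| Power, adjust if imbalanced | 80.1% | 80.2% |
| Power, always adjusted | 81.9% | 85.5% |

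The simulation error is about 0.4 points for power and 0.2 for overall type I error. The rows given imbalance rest on only about 600 runs each (5% of 12,000), so their error is about 1 point. At OR 1.65 the crude and adjusted figures there are not distinguishable.

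Further runs that included an OR of 2.0 gave always-adjusted power of 81%, 83% and 86% for ORs of 1.65, 2.0 and 2.7. Chi-square stayed at about 80%, and two-stage type I error was 4.9% to 5.1%.

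**4. Does the missing ranking matter?** In runs at 30% v 40% in which the switch was thrown, the crude and adjusted tests disagreed on significance in 14%, 20% and 22% of trials for the three ORs.

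**The case against.** **The chi-square test is unconditional.** It is always performed, and the sample size reproduces from it. A reader might infer that the primary test itself is chosen by the data. The text does not support that. What is data-driven is whether an adjusted model exists, what it contains, and which estimate is then treated as final. A fuller plan may rank the two, but the stated trigger would remain.

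**Type I error.** A reader might also infer that the two-stage rule inflates the error rate. It does not: 4.4% to 5.1% across the runs, and 4.9% even if the better of the two results is taken whenever imbalance occurs. The 12% figure is conditional. It applies to the crude test in the trials where a strong predictor is imbalanced, and it does harm only if the crude result is then relied on.

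**The 5% trigger is partly inferred.** The logistic sentence names no test. The link to the baseline comparisons is the natural reading, not a stated one. The Cox sentence could mean significance for the outcome. That is still data-driven, but strong predictors would then usually enter, and the 5% figure would not apply to time to healing.

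**Prognostic strength is not documented.** This stands. It is plausible for initial area, since area is recorded as part of the PUSH scale on which healing is scored, but the odds ratios are assumptions.

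**The power loss is modest.** This also stands. An unadjusted analysis of a randomised trial is valid. If all 410 per arm are analysed, as the intention-to-treat section plans, the crude test already has about 85% power, and adjustment adds about 1 to 6 points.

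**Percentage change in area.** A reader might extend the point to this endpoint, where initial area serves only as the denominator. Every healed ulcer scores exactly 100%, which creates ties. But the endpoint is secondary, and a Mann-Whitney test is already planned for non-normal data. Covariance analysis would be a preference there, not a correction.

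**Conclusion.** The point holds in a bounded form. The article makes adjustment of the logistic and Cox analyses depend on observed imbalance or significance and does not rank crude against adjusted.

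- **Selection by chance.** On the 5% between-arm reading, a given predictor is adjusted for in about 5% of trials, and some adjustment is triggered in 23% to 46% (5 to 12 independent variables, assumed).
- **Unranked results.** When the switch is thrown, the two results can differ on significance in roughly a fifth of trials or fewer.
- **Conditional error.** For a strong predictor (OR 2.7 per SD, assumed), the crude test has about 12% type I error given imbalance, against about 4% to 5% adjusted. For a weak predictor there is no visible difference.
- **Power.** About 1 to 6 points are forgone at 348 per arm, and the plan's rule recovers almost none of that.

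Overall type I error is not at issue. The change is worth making because it costs little and removes a choice that would otherwise be made after seeing the data.

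**What to change.** 1. Drop baseline significance tests as the trigger for adjustment, and describe baseline balance without p-values.
2. Prespecify one primary logistic model for healing, fitted whatever the observed balance: arm plus a short list from Visit 1, for example log initial area or baseline PUSH score, Braden score and care setting.
3. Handle centre as a random effect or conditional stratum, not as fixed dummies. With at most 24 patients per centre, 820 patients need at least 35 centres (820/24 = 34.2). In simulation with no true centre effect, fixed centre terms inflated the treatment log odds ratio by about 6% with 35 centres of 20, and about 13% with 68 centres of 10.
4. Report the standardised risk difference, relative risk and number needed to treat from that model with 95% confidence intervals. The article already plans these measures but does not say which model they come from.
5. Keep the chi-square test as supportive, and say so.
6. Use the same patient-level covariates in the Cox model.

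Optionally, analyse final area with initial area as a covariate instead of percentage change.

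The cost is wording and a slightly more complex primary model. The patient-level variables are already collected and the 410 per arm is unchanged.

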#### Exclusion criteria

Stage I, III or IV PrU only.

Non classifiable PrU.

Surgical treatment prior to PrU and/or PrU in previously irradiated areas.

Participation in another clinical trial within 3 months of study entry.

Allergy or hypersensitivity to materials in the study dressings.

Signs of PrU basal infection (sepsis/bacterial), cellulitis or osteomyelitis. Patients successfully treated for infection can be included if the PrU can be classified as stage II.

Venous ulcers and/or diabetic feet.

Type I diabetes.

Situations of extreme severity and/or agony; e.g. patients in terminal phase with <3 points on the Braden scale and/or a life expectancy < 1 month.

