### Withdrawal criteria

Patients will be removed from the trial if any of the following conditions are met:

•Infection and/or progression of PrU-II

•Disease progression, requiring discontinuation of the investigational product treatment regimen or study requirements.

•An adverse event (AE) that requires discontinuation of the investigational product or study procedures.

•Voluntary withdrawal

•Loss of follow-up

Protocol deviations will be registered. In case of a serious protocol deviation, the research team will assess the possibility of withdrawing the patient from the study.

Study discontinuations must be registered in the CRF, and, where possible, tests and procedures usually performed at the final visit (visit 8 or end of study) should be carried out. Patients who withdraw due to AEs must be followed until the end of the study (8 weeks), and if necessary until AE resolution.

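### If patients removed for infection or ulcer progression are censored at exit, the planned Kaplan-Meier analysis of time to healing overstates how many ulcers heal by week 8 (secondary outcome)

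*Protocol article*

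**What the plan says.** Under Comparative analysis the protocol article fixes the estimator and the test: "Time to healing in the two treatment arms will be calculated by the Kaplan-Meier method and compared using the log-rank test". It adds: "A Cox regression model of proportional risks will be used when the models require adjustment for any statistically significant baseline variable". Aim and hypothesis lists time to healing among the secondary objectives.

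The Withdrawal criteria remove patients for, among other reasons, "Infection and/or progression of PrU-II" and "Disease progression, requiring discontinuation of the investigational product treatment regimen or study requirements". For a patient who meets a withdrawal criterion before week 8, the Work plan says: "The nurse will perform all the activities described for the earlier visit, as well as those described for Visit 8". Continued observation is required for one group only: "Patients who withdraw due to AEs must be followed until the end of the study (8 weeks".

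The ITT section bases all calculations on the randomised patients, "including all patients randomized, whether treated or not, and including all patients who have withdrawn prematurely". Death is not in the list of withdrawal reasons. The relevant exclusion covers patients in extreme or terminal condition, including those with "a life expectancy < 1 month". The article does not say how any of these exits enters the time-to-healing analysis.

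**The concern.** Kaplan-Meier knows two outcomes, event or censored. A patient removed because the ulcer became infected or progressed has not healed, so without a special rule that patient is censored on the day of removal. Censoring assumes that the patient would have gone on to heal at the same rate as those who stayed. Here the reason for leaving is that the ulcer got worse, so the assumption is doubtful and the censoring is informative.

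Two things are at stake. First, the healing curve at week 8 would read higher than the share of patients who actually healed, and the same report could carry two different healed percentages for one arm. Second, if one dressing loses more ulcers to infection or progression, the time-to-healing comparison could look better for that dressing than the number healed warrants. The dressings cannot be masked (Blinding section) and the withdrawal decision is made in the open, so unequal removal between arms is possible, though nothing in the article shows that it will occur.

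**Working it through.** **Inputs.** From Sample size: 30% healed at 8 weeks on polyurethane, a 10-point difference, two-sided alpha 5%, power 80%, 15% loss, 410 per arm. From the Work plan: 8 weeks of follow-up with 8 visits. Assumed, because the article gives no figure: failures (infection, progression or death) of 5% to 25% by week 8, constant cause-specific hazards, no healing after removal, and no other loss.

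**The plan's own figure.** For 30% v 40%, with mean 0.35:

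n = [1.96·√(2·0.35·0.65) + 0.8416·√(0.30·0.70 + 0.40·0.60)]² / 0.10² = 356 per arm, and 356 × 1.15 = 409.4, rounded up to 410.

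The stated 410 is reproduced. It concerns the primary proportion; no event count or power is given for time to healing.

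**Step 1: the healing curve.** Let h be the true proportion healed by week 8, f the proportion failed, and F = h + f. The total cumulative hazard is H = −ln(1 − F), of which healing takes the share s = h/F. With failures censored, 1 − KM at week 8 is 1 − exp(−s·H).

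| h | f | H | s | 1 − KM | Overstatement (points) |
|---|---|---|---|---|---|
| 30% | 5% | 0.431 | 0.857 | 30.9% | +0.9 |
| 30% | 10% | 0.511 | 0.750 | 31.8% | +1.8 |
| 30% | 15% | 0.598 | 0.667 | 32.9% | +2.9 |
| 30% | 20% | 0.693 | 0.600 | 34.0% | +4.0 |
| 40% | 5% | 0.598 | 0.889 | 41.2% | +1.2 |
| 40% | 10% | 0.693 | 0.800 | 42.6% | +2.6 |
| 40% | 15% | 0.799 | 0.727 | 44.1% | +4.1 |

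**Step 2: the comparison, equal true healing of 30%, failures 20% v 10%.** The healing hazards are in the ratio (0.600 × 0.6931)/(0.750 × 0.5108) = 0.4159/0.3831 = 1.086, in favour of the arm with more failures. Healings: 410 × 0.30 × 2 = 246. Shift in z: ln(1.086) × √246 / 2 = 0.64. Two-sided rejection: P(Z > 1.96 − 0.64) + P(Z < −1.96 − 0.64) ≈ 0.094 + 0.005, about 10%.

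**Step 3: simulation** (410 per arm, weekly visits, 1,500 runs, so a standard error of about √(0.05 × 0.95/1500) = 0.6 points near 5%). Log-rank rejection with 30% true healing in both arms:

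| Failures | Censored at exit | Kept unhealed to week 8 |
|---|---|---|
| 5% v 5% | 4.0% | 4.3% |
| 15% v 15% | 4.8% | 4.5% |
| 5% v 15% | 7.8% | 4.9% |
| 10% v 20% | 9.3% | 6.3% |
| 5% v 25% | 19.5% | 4.7% |

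The last column averages (4.3 + 4.5 + 4.9 + 6.3 + 4.7)/5 = 4.9%.

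**Step 4: a real difference, 30% v 40% healed.** If the better arm also fails less (15% v 5%), power is 70% censored and 85% kept at risk. If it fails more (5% v 15%), power is 97% and 87%.

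**The case against.** The strongest reply is that the article never says these patients are censored at exit. Kaplan-Meier is compatible with keeping failures at risk as unhealed to week 8, the ITT statement includes early withdrawals, and a censoring rule is commonly left to the full protocol or SAP. This stands in part: a reader might infer that the plan prescribes uninformative censoring, and it does not. But ITT says who is analysed, not how a removed patient's time is handled, and a patient censored at week 3 is still included. Follow-up to week 8 is required only after AE withdrawal; for other exits the final visit is done on leaving. The named method in its ordinary form therefore does not fit the removal rule.

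Second, infection is not a permanent bar to healing: the Exclusion criteria admit patients whose infection was successfully treated. That is fair. Counting removal as failure is a choice of estimand, and healing seen afterwards should not be discarded.

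Third, a reader might call the 10% a false-positive rate. That goes too far. Log-rank with these exits censored validly tests equality of cause-specific healing hazards, and in the example those hazards do differ. The 10% is an error rate only against the hypothesis that equal proportions heal.

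Fourth, a reader might take deaths as expected. The exclusion only leaves them possible, and no mortality figure is given. The point holds on infection and progression alone.

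**Conclusion.** The concern holds in a limited form. Removal for infection or progression, combined with Kaplan-Meier under ordinary censoring at exit, overstates healing by week 8 by about 1 to 3 points when 30% truly heal and 5% to 15% fail. These failure rates are assumptions, with the upper end equal to the whole planned loss of 15%. If some removed patients heal later within the 8 weeks, the overstatement is smaller.

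Between arms, distortion needs unequal failures. At similar healing rates the overstatement is larger in the arm with more failures, but this is not a general law, because the bias also grows with healing: 40% healed with 10% failures gives +2.6 points, while 30% healed with 13% failures gives 1 − exp(−(0.30/0.43) × 0.562) = 32.4%, or +2.4.

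Only a secondary outcome is touched. The primary chi-square test and the sample size do not depend on censoring.

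**What to change.** In Comparative analysis, report time to healing as the cumulative incidence of healing (Aalen-Johansen) and compare arms with Gray's test, taking removal for infection or progression, and any death, as competing events. Alternatively, keep these patients in the risk set as unhealed to week 8; with no other loss and no later healing counted, this gives the same estimate. Where follow-up continues after removal, use any healing that is observed, on a rule consistent with the primary healed percentage. Censor only true loss to follow-up and voluntary withdrawal. Keep log-rank and Cox as supporting analyses, labelled as cause-specific.

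The cost is a little more analysis work. The reason and date of exit must be captured: the article says that discontinuations are registered in the CRF but does not name these two items, so the form should be checked. Patients, visits and sample size do not change.
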